## Abstract

**Background:**

Traumatic cervical spinal cord injury (SCI) results in reduced sensorimotor abilities that strongly impact on the achievement of daily living activities involving hand/arm function. Among several technology-based rehabilitative approaches, Brain-Computer Interfaces (BCIs) which enable the modulation of electroencephalographic sensorimotor rhythms, are promising tools to promote the recovery of hand function after SCI. The “DiSCIoser” study proposes a BCI-supported motor imagery (MI) training to engage the sensorimotor system and thus facilitate the neuroplasticity to eventually optimize upper limb sensorimotor functional recovery in patients with SCI during the subacute phase, at the peak of brain and spinal plasticity. To this purpose, we have designed a BCI system fully compatible with a clinical setting whose efficacy in improving hand sensorimotor function outcomes in patients with traumatic cervical SCI will be assessed and compared to the hand MI training not supported by BCI.

**Methods:**

This randomized controlled trial will include 30 participants with traumatic cervical SCI in the subacute phase randomly assigned to 2 intervention groups: the BCI-assisted hand MI training and the hand MI training not supported by BCI. Both interventions are delivered (3 weekly sessions; 12 weeks) as add-on to standard rehabilitation care. A multidimensional assessment will be performed at: randomization/pre-intervention and post-intervention. Primary outcome measure is the Graded Redefined Assessment of Strength, Sensibility and Prehension (GRASSP) somatosensory sub-score. Secondary outcome measures include the motor and functional scores of the GRASSP and other clinical, neuropsychological, neurophysiological and neuroimaging measures.

**Discussion:**

We expect the BCI-based intervention to promote meaningful cortical sensorimotor plasticity and eventually maximize recovery of arm functions in traumatic cervical subacute SCI. This study will generate a body of knowledge that is fundamental to drive optimization of BCI application in SCI as a top-down therapeutic intervention, thus beyond the canonical use of BCI as assistive tool.

**Trial registration:**

Name of registry: DiSCIoser: improving arm sensorimotor functions after spinal cord injury via brain-computer interface training (DiSCIoser). Trial registration number: NCT05637775; registration date on the ClinicalTrial.gov platform: 05-12-2022.

## Background

Traumatic Spinal Cord Injury (SCI) represents a devastating condition for physical and social well-being [1]. It is increasingly recognised as a global health priority due to the complex and expensive medical treatment required [2]. Despite numerous neuroprotective and neuroregenerative strategies recently proposed [3], there is still no consistent approach to this complex and multifaceted clinical condition [4].

Over the last decade, the epidemiology of traumatic SCI has progressively changed with an increase in cervical lesions, particularly at C1-C4 levels [5]. Depending on the level and severity of injury [6], arm and hand functions are impaired to varying degrees. Reduced upper extremity ability compromises the completion of activities of daily living. Therefore, recovery of arm/hand function is highly valued by individuals with cervical lesions and is considered the most important factor in improving their quality of life [7–9].

Technological advances have led to the development of novel interventions aimed at improving upper arm function in individuals with SCI [10, 11], and advances in neuroimaging techniques have provided evidence of structural and functional reorganization of the brain after traumatic SCI in both animal models [12] and humans. The potential role of such remote brain reorganization in promoting sensorimotor functional recovery has been widely emphasised [13–15], but there is still a limited number of studies investigating the effects of arm and hand function training in individuals with cervical SCI.

Current rehabilitation approaches after traumatic SCI mainly consist of intensive training of lost or impaired function that is assumed to increase the activity-dependent plasticity of spared circuits and thus leading to functional improvements [16]. Recently, neuromodulatory interventions targeting the sensorimotor systems at various levels have been applied in humans with SCI in combination with training to improve functional recovery [17–19]. Neurological rehabilitation of SCI may also benefit from cognitive training based on motor imagery (MI) [20], which allows active stimulation of brain motor areas promoting brain plasticity associated with positive effects on motor performance [21–23].

In the effort of encouraging the top-down contribution of supraspinal sensorimotor signal in SCI rehabilitation, the Brain-Computer Interface (BCI) technology [24] may provide fundamental tools not only for the restoration but also for the recovery of sensorimotor function. The long history of BCI research in SCI has been substantially devoted to developing systems to control external devices to restore function [25–27]. However, recent findings indicate that non-invasive BCI training in combination with intensive rehabilitation may be useful for individuals with chronic SCI to recover gait [28] and arm function [29].

The main evidence for the efficacy of non-invasive BCIs as neurorehabilitation tools stems from clinical trials conducted on stroke population, in which BCI-assisted MI training was shown to be effective in promoting brain plasticity, resulting in improved hand motor function [30]. These promising findings corroborate the idea that a low-cost technique such as electroencephalography (EEG)-based BCIs can be exploited to optimize the delivery of MI based rehabilitation interventions beyond stroke.

Moreover, despite differences in the usual mechanism of injury between stroke (ischaemia) and SCI (trauma), rehabilitation approaches could successfully translate in similar recovery of sensorimotor functions between ischaemic and traumatic SCI [31]. Furthermore, in both stroke and SCI, neuroplasticity may be considered the key to overcoming the injury-induced loss of central nervous system tissue and the resulting sensorimotor deficits [16].

For this reason, it could be assumed that monitoring and modulating the central nervous system plasticity occurring after a SCI is a key factor in shaping clinically valuable top-down rehabilitation strategies with the aim to recover sensorimotor function after SCI. In the DiSCIoser study, we propose to use a goal-oriented action imagination training, controlled, and objectified by means of a BCI system. As such, the BCI based motor imagination training would engage the sensorimotor system and thus facilitate neuroplasticity to eventually optimize upper limb sensorimotor functional recovery in patients with SCI during the subacute phase when brain and spinal plasticity is at its peak.

### Aim and hypotheses

The “DiSCIoser'' study is a randomized controlled trial (RCT) designed to provide evidence for a significant improvement of hand sensorimotor function induced by a BCI-assisted MI training in patients with traumatic SCI.

Based on our previous findings on the efficacy of BCI-supported MI training in patients with stroke [30], we hypothesise that establishing a real-time contingency between the content of MI and an ecological feedback specifically designed to train MI in patients with SCI will boost the effect of MI training in engaging the sensorimotor system, promoting meaningful cortical sensorimotor plasticity and eventually maximizing recovery of hand function.

Accordingly, the aim of the RCT will be to determine whether the BCI-assisted MI (BCI-MI) training, administered by means of a BCI system fully compatible with a clinical setting, is superior to a non-BCI assisted MI (Control-MI) training in improving hand sensorimotor function outcomes in individuals with traumatic cervical SCI admitted to the ward “Centro Spinale” at Fondazione Santa Lucia for their standard rehabilitation care.

## Methods/design

A total cohort of 30 participants will be enrolled and randomized in a single centre, single blind RCT to investigate the efficacy of BCI-MI training for hand movements, delivered during the subacute phase of SCI (hospitalization period). The primary and secondary outcome measures collected from participants assigned to BCI-MI training will be compared with those of participants who receive an equivalent dose of MI training without BCI support (Control-MI).

All procedures conducted in this trial follow national institutional ethical standards and the Helsinki Declaration. The study protocol and related procedures were approved by the institutional review board: the Independent Ethical Committee of the Fondazione Santa Lucia (FSL), I.R.C.C.S., Rome, Italy (protocol CE/PROG.884 15-12-2020). The trial was registered on the clinicaltrials.gov in 05-12-2022 (trial registration number: NCT05637775).

### Study design

The DiSCIoser trial is designed as a randomized, controlled, assessors blinded single-centre trial with 2 parallel groups with 1:1 allocation ratio. The study flow is illustrated in Fig. 1. The participants recruitment, intervention delivery and data collection will take place at the Spinal Unit of FSL (Rome, Italy). Upon admission, patients with subacute cervical SCI will be screened for eligibility criteria by the project’s clinical staff (neurologists) according to the inclusion criteria of the study. Eligible participants will be introduced to the study protocol by authorized personnel, and they will be presented with the informed consent. Participants are randomized (within one week of first contact with the participants) to one of 2 intervention groups (as add-on): the BCI-MI training (experimental condition) or the Control-MI training (control condition).

**Fig. 1 Fig1:**
[figure not shown]
DiSCIoser Randomized Controlled Trial summary. All Spinal Cord Injury (SCI) patients admitted to the Spinal Unit at Fondazione Santa Lucia IRCCS will be screened (T enrol) for eligibility according to Inclusion/Exclusion criteria. The evaluation according to the International Standards for Neurological Classification of SCI (ISNCSCI) ASIA Impairment Scale (AIS) and the predicted mean Upper Extremity Motor Score (UEMS) recovery will be used for eligibility. Eligible participants will be presented with the Informed Consent and recruited (30 participants). Clinical, neuropsychological, neurophysiological and neuroimaging assessments will be performed before (T pre) and after (T post) the intervention

The primary outcome is the Graded Redefined Assessment of Strength, Sensibility and Prehension (GRASSP) somatosensory sub-score [32]. Secondary outcomes are the GRASSP motor sub-score, the self-care section of the Spinal Cord Independence Measure (SCIM) [33] scale and a battery of clinical/functional scales (See Table 1 for details) to monitor upper limb muscle strength, tone, pain, and functional ability. Other pre-specified outcome measures are extracted from neuropsychological, neurophysiological and neuroimaging assessment before and after training. The overall outcome assessments are detailed in the Assessment section. The outcome assessors are blinded to the treatments.

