### Sample size

The sample size was calculated on the hypothesis that experimental intervention (BCI-MI training) is superior in improving the primary outcome measure. Based on preliminary findings in the Upper Extremity Motor Scores (UEMS) from the International Standards for Neurological Classification of SCI (ISNCSCI) ASIA Impairment Scale (AIS) [35] in experimental vs control condition, alpha level at 0.05, statistical power at 80%, and one-tailed t-test, 15 participants per group (Control-MI and BCI-MI) are needed. The analysis was performed using the statistical software STATISTICA 8.0 (Stat Soft. Inc. 1984–2007, USA) according to the algorithm implemented in the tool Power Analysis/Sample Size Calculation.

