### Inclusion/exclusion criteria

The specific Inclusion and Exclusion criteria are listed below:

Inclusion criteria:age between 18 and 70 years,current hospitalization at FSL site for rehabilitation care,subacute traumatic cervical SCI (30–90 days after the event),classification according to ISNCSCI ASIA Impairment Scale A-D,lesion level between C1 and T1,predicted average UEMS recovery of less than 40/50 [36].

Exclusion criteria:other conditions (present or previous) potentially affecting sensorimotor function of the upper extremities,significant traumatic brain injury,history of epilepsy or previous neurological deficits,psychiatric or cognitive comorbidities involving motor planning problems or impulsivity (unable to follow commands),inability to give informed consent and understand training requirements,concurrent enrolment in other clinical research trials focusing on specific unconventional treatments targeting upper limb function.

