#### Secondary

The secondary outcome measures are the changes from pre- $$({T}_{pre})$$ to post- $$({T}_{post})$$ of the following fields and assessment scales:muscle strength: the GRASSP motor score of bilateral arms that ranges from 0 (maximum impairment) to 50 (normal) for each side [32]; the UEMS and the Lower Limb Motor Score (LEMS) from the ISNCSCI AIS evaluation for the residual strength assessment in upper and lower limb segments, it ranges from 0 to 25 for each arm and leg [35]; the arm will be considered as dominant and non-dominant according to the results of the Edinburgh Handedness Inventory [37];muscle tone: the Modified Ashworth Scale (MAS) for the muscle tone assessment of upper and lower limbs [38] ranging from 0 (absence of augmented muscle tone) to 4 (non-reducible spasticity); the Penn Spasm Frequency Scale (PSFS) for the self-assessment of upper and lower limb spasms frequency (ranging from 0, absence of spasms, to 4, more than 10 spasm each hour) and severity (ranging from 1, mild, to 3, severe) [39];pain: the International SCI Pain Basic Dataset (ISCIBPDS) for pain assessment; a pain-intensity, rating from 0 to 10, quantifies pain impact on activities daily living, humour, and sleep functions [40];functional ability: the GRASSP prehension ability ranging from 0 to 12 for each side and prehension execution ranging from 0 to 20 for each side; the Spinal Cord Injury Independence Measure (SCIM) self-care section score ranges from 0 (maximum impairment) to 20 (independence) [33].

Other specified secondary outcome measures will be extracted from neurophysiological, neuroimaging, neuropsychological and user experience assessments (see below).

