### Randomization procedure and methods

The random allocation sequence of participants to experimental (BCI-MI training) or control (Control-MI training) intervention groups will be generated by using Matlab (The MathWorks Inc, Natick, Massachusetts, USA, release 2019a).

The randomization sequence will be stratified by age (2 categories: ≤ 50 years old and > 50 years old) [61] and by GRASSP somatosensory scores (2 categories: ≤ 8 and > 8). A 1:1 allocation ratio will be used. For each stratum, the sequence will include 30 random allocations. The allocation sequence is securely stored at FSL. Randomization of participants will stop after randomization of the 30th participant in the study by summing participants in all strata.

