#### Secondary analyses

All secondary outcomes will be compared between groups. T-test for independent samples and non-parametric tests will be used for continuous and categorical data, respectively. Further explorative analyses will be carried out on primary and secondary outcomes in subgroups of participants identified by strata used in randomization procedure. The statistical methods adopted for primary and secondary analyses will be used. All analyses will be under the expert supervision of the partner SAP.

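### UEMS change is compared without adjustment although baseline UEMS and the predicted UEMS recovery used for entry are available for every participant: valid, but less precise than it could be

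*Protocol article*

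**What the plan says.** - **Prediction at entry.** The caption of Fig. 1 states that "predicted mean Upper Extremity Motor Score (UEMS) recovery will be used for eligibility". Inclusion/exclusion criteria sets the limit: "predicted average UEMS recovery of less than 40/50". Every randomised participant should therefore have a predicted value. The article mentions it nowhere else.
- **UEMS as outcome.** Under Secondary, the muscle strength outcomes include "the UEMS and the Lower Limb Motor Score (LEMS) from the ISNCSCI AIS evaluation for the residual strength assessment in upper and lower limb segments". The outcome is the change from T_pre to T_post, with 0 to 25 points per arm. T_pre is placed at randomisation, before training starts.
- **Analysis.** Secondary analyses says: "T-test for independent samples and non-parametric tests will be used for continuous and categorical data, respectively". No covariate is named. The only further use of prognostic information is exploratory subgroups defined by the randomisation strata.
- **Randomisation.** "The randomization sequence will be stratified by age" and by GRASSP somatosensory score, so not by predicted or baseline UEMS.
- **Sample size.** The 15 per group comes from preliminary UEMS findings, with alpha 0.05, 80% power and a one-tailed t-test. No difference or SD is given.

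**The concern.** Participants enter 30 to 90 days after injury, with AIS grades A to D and lesions from C1 to T1, and then train for 12 weeks. Recovery over that time is likely to differ widely between them whichever training they receive. The sponsor relies on a prediction of UEMS recovery to decide who enters, then leaves it out when comparing the arms on that same scale. Baseline UEMS enters only through the subtraction.

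What is at stake is precision. Whatever part of UEMS change these two values explain stays in the error term. With 15 per arm, the difference between arms in any standardised baseline value has a standard error of sqrt(2/15) = 0.37 SD. A gap above 0.5 SD (0.5/0.365 = 1.37 standard errors) would therefore arise in about 17% of simple randomisations. The unadjusted estimate cannot correct for such a gap.

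**Working it through.** **1. The plan's own figure.** Fifteen per arm cannot be reproduced forwards, because the article gives no UEMS difference or SD. Solved backwards with the noncentral t distribution (df = 28, noncentrality d × sqrt(15/2), one-sided critical value 1.701), 80% power requires d = 0.93. With the normal approximation, d = 0.93 one-sided returns 15 per arm.

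**2. Unadjusted two-sided test.** Primary analyses specifies two-tailed testing; I assume the same for the secondary outcomes. At d = 0.93 the noncentrality is 0.931 × 2.739 = 2.55 and the critical value is 2.048. Power is 69%.

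**3. With covariates.** If k covariates explain a share R² of the variance of change, the standardised effect becomes d / sqrt[(1 − R²) × c]. Here c allows for chance covariate imbalance, c = 1 + k/(N − k − 3) with N = 30, and df = 28 − k. For one covariate c = 1 + 1/26; for two, c = 1 + 2/25. R² is an assumption; the article gives nothing from which to derive it.

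| Assumed R² | One covariate (df 27) | Two covariates (df 26) |
|---|---|---|
| 0% | 67% | 66% |
| 10% | 72% | 70% |
| 20% | 77% | 75% |
| 30% | 82% | 81% |
| 40% | 88% | 86% |

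The comparator is 69%. Two covariates break even at a joint R² of about 8%, one at about 4%. The largest loss with two is 69.2 − 65.6 = 3.6 points.

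**4. Why baseline UEMS belongs in the model.** A limit of 40 out of 50 is on the full two-arm UEMS scale (2 × 25), so it reads most naturally as a predicted attained score. The outcome is change. A participant predicted to reach 38 may start at 35 or at 15. To illustrate, let baseline B and predicted final score F have equal SDs (set to 1) and correlation ρ, and let change = F − B + e, where e has SD s. Then:

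- Variance of change = 2 − 2ρ + s².
- R² from the prediction alone = (1 − ρ)² / variance.
- R² from prediction and baseline together = (2 − 2ρ) / variance.

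With ρ = 0.7 and s = 0.3, the variance is 0.69. The prediction alone explains 0.09/0.69 = 13%, and both together 0.60/0.69 = 87%. With ρ = 0.9 and s = 0.7, the variance is again 0.69. The prediction alone explains 0.01/0.69 = 1%, and both together 0.20/0.69 = 29%. Over ρ from 0.7 to 0.9 and s from 0.3 to 0.7, the prediction alone thus explains roughly 1% to 13%, and the pair 29% to 87%. These inputs are assumed and treat the prediction as well calibrated. They show why the pair is needed, not how large the gain will be.

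**The case against.** The strongest reply is that nothing here is an error. A two-sample comparison of change scores in a randomised trial is valid, and its standard error already allows for chance imbalance. That stands. A reader might infer from the missing covariates that the UEMS result would be biased; the documents do not support that. Stratification by age and GRASSP somatosensory score may also balance some prognosis indirectly.

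A second reply is that the prediction may be a weak covariate. The article speaks of a predicted mean or average and cites a source not at hand, so the value may be a coarse group figure rather than an individual forecast. The entry limit also narrows its range. That stands too. It would be wrong to infer that the prediction alone would remove most spontaneous recovery, or that adjusting is free.

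A third reply is that UEMS is one secondary outcome among many. The article also lists GRASSP motor score, prehension ability and execution, SCIM self-care and motor evoked potentials. This limits the weight of the point.

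The reply that an unseen analysis plan may settle the matter is weaker, because the article itself names the test for secondary outcomes and it is an unadjusted one.

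**Conclusion.** The point holds as one of efficiency. The article names an unadjusted test for UEMS change while two relevant pre-training values are at hand for every participant. At the implied effect of 0.93 SD with 15 per arm, two-sided power is 69% unadjusted. With both covariates it is about 66% to 86% over an assumed joint R² of 0% to 40%. Adjustment pays if the pair explains more than about 8% of the variance of change, and costs at most about 4 power points otherwise.

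These figures assume a t-test on roughly normal changes, two-tailed testing of secondary outcomes and all 30 participants analysed. The true R² is unknown. No gain is shown for the primary GRASSP somatosensory score, and none should be inferred. The change is worthwhile but optional.

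**What to change.** In Secondary analyses, state that UEMS will be compared between arms with a linear model of T_post UEMS (or its change) on arm, baseline UEMS at T_pre and the predicted UEMS recovery used for eligibility, reporting the adjusted difference with its 95% confidence interval. State also whether the prediction is an attained score or a gain, and whether it is individual or group-level. Keep the unadjusted comparison as a supporting result if wanted.

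The cost is a sentence or two in the plan and two degrees of freedom. No participants, assessments or changes to care are added. It should be fixed before outcomes are unblinded; added later, the choice of covariates would look driven by the data.

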**Table 1 Tab1:**
[figure not shown]
Standard protocol items as recommended for Interventional Trials (SPIRIT)

The study is presented according to the Standard Protocol Items: Recommendations for Interventional Trials (SPIRIT) [34]. Table 1 shows the SPIRIT schedule of enrolment, interventions, and assessments.

